### Quality assurance: Investigator team

The investigator team will be composed of two movement disorders MDS-UPDRS certified neurologists, two movement disorder nurses, two occupational therapists, one psychologist, one health-economist (Hospital Universitario of Burgos, Spain), and four computer engineers (University of Burgos, Spain).

### Study timetable

Pre-start procedures: January-June 2020.First assessment: July 2020-December 2021.Data analysis: August-September 2022.Report and publications: years 2021–2022.

## Procedure

After signing the informed consent form, investigators will invite PD patients to participate in this randomized controlled trial. Patients will be randomly assigned using a block gender-randomization Excel calculator [male/female: intervention/control groups), providing an equal number of males and females with PD in the control/intervention groups (1:1). There will be no personal expenses for the participant during the study; instead, all assessments will be free, including the neurologist, nurse, psychologist, and occupational therapist evaluations. The patients will be contacted by phone to confirm they attended the treatment sessions. Likewise, reports of the assessments performed during the study will be available to improve patient adherence to the intervention protocols.

Two study phases will be established (Fig 1). In the *first phase* (baseline-4^th^ month), short-term benefits will be assessed. All participants will be evaluated at baseline and four months in office. Patients allocated in the intervention group will be receiving the telemedicine fall prevention program. The occupational therapist will bring the equipment for videoconferencing to the patients’ home, set up the room for physical therapy, and evaluate the patient’s risk of performing different exercises according to the patient’s capabilities and home environment. In the *second phase* (5^th^-8^th^month), long-term benefits will be assessed. All patients allocated in the intervention group will discontinue the telemedicine program at the end of the 4^th^ month. All patients will receive standard medical care provided by the movement disorder neurologist and nurse, with a final visit at eight months from baseline.

**Fig 1 pone.0260889.g001:**
[figure not shown]
One-year, randomized, case-control, single-blinded intervention study.

### In-office visits (best standard medical care)

Patients will be evaluated in-office at baseline, four months, and eight months. At baseline, we will collect information on socio-demographics (age, gender, education background, living status (urban vs. rural, alone vs. with family), and PD clinical characteristics (PD duration, drugs). In each in-office visit, we will perform a complete physical and neurological exam and will complete a standard PD follow-up visit. Consensus-based clinical practice recommendations for the examination and management of falls in patients with PD will be assessed [27]. We will evaluate vital signs (standing and lying down blood pressure), heart pulse, oximetry, falls history (number, characteristics, place), visual acuity (eye chart), nutritional and dysphagia screening, balance, and strength by dynamometry. Fall prevention will be performed by providing pharmacological and non-pharmacological therapy adjustments, education, nutritional interventions, and referrals to other physicians if needed (Fig 2).

**Fig 2 pone.0260889.g002:**
[figure not shown]
Telemedicine multidisciplinary approach for falls prevention in Parkinson´s disease.

### Virtual visits

Telemedicine visits in the intervention group will include telerehabilitation, neurologist and nurse telecare, and tele-support groups conducted by the psychologist (Fig 3). Tele-rehabilitation will consist of an individualized program with each of the patients, 45 to 60 minutes long. All sessions will be directed and supervised in real-time by the occupational therapist. During these telerehabilitation sessions, the occupational therapist will give the patient the necessary instructions to perform various exercises. First, a prior physical warm-up, consisting of a series of mobility exercises and stretching, followed by exercises designed to improve body posture, increase mobility, favor transfers, reduce axial stiffness, freezing, and walking disturbances, and enhancing balance and coordination, according to the cognitive, sensory-motor training therapy (Perfetti method) [28, 29]. During this cognitive sensory-motor training therapy, motor control will be improved using a specific type of repetitive sensory and motor re-learning protocol. Different exercises will be accommodated based on the patient’s capacity, including kinesthetic tasks [simple to complex parameter movement discrimination] with the corresponding cognitive activity [recognition of the direction and distance of the movement], and coordination tasks associated with executive cognitive activity [28, 29].

**Fig 3 pone.0260889.g003:**
[figure not shown]
Schematic view of video data information using artificial intelligence.

As a secondary objective, the occupational therapist will provide education to promote behavioral changes toward healthy lifestyles such as environment modifications, daily walks, social activities, and healthy eating behaviors. In addition, the nurse and the neurologist will conduct monthly video conferences with the patient (10–15 minutes duration each one approximately). During these visits, fall history and characteristics and medical management medications adjustments, education, nutritional interventions, and referrals if needed) will be performed. Group support interventions (fear of falling, caregiver burden) will be conducted every month by the psychologist to patients and caregivers separately.

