### Blinded, remote motor assessments

In all participants, we will collect waist-worn wearables data reporting On and Off states (with and without dyskinesias), gait parameters, falls and FOG using the STAT-ON™, once a month during the eight months duration of the study.

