### Statistical analysis

The study includes several necessary methodological resources that will minimize the risk of bias, such as the randomization process, allocation concealment, blinded assessment of the results, and intention-to-treat analysis. A statistician blinded to group allocation will supervise the data entry and analysis. The normality of the variables will be evaluated using the Kolmogorov-Smirnov test and graphs, including histograms and normal distribution plots. For the description of the quantitative variables, the mean and the standard deviation will be used, and for categorical variables, the frequency distribution and percentages. For non-normally-distributed variables, we will use the median, the interquartile range, and the corresponding non-parametric tests. The association between independent categorical variables will be analyzed using the χ2 test or Fisher’s exact test. The means between the two groups will be compared using the one-way analysis of variance (ANOVA). We will analyze the relationship between quantitative variables using correlation coefficients.

We will use logistic regression models to analyze the relationship between fall strategy prevention of 50% reduction in the incidence of falls (yes vs. no) as the dependent variable with the intervention vs. the control group, as the independent variable adjusted for age, gender, total motor MDS-UPDRS, comorbidity severity, and total levodopa equivalent dose. Other pertinent univariate and multivariable analyses will be performed based on the objective type. Also, given the complexity of potential analysis, including a diversity of variables from different origin and measurement properties, advanced statistical methodology (data mining, AI techniques) will be applied as needed. The level of significance will be set at p < 0.05. Statistical analysis will be performed with SPSS V.25.0. (IBM SPSS Statistics for Windows, Armonk, NY, USA).

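### For the first four months only the intervention arm is asked about falls every month, and the source of the primary fall count is not fixed, so the count can differ by arm through ascertainment.

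*Protocol article*

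**What the plan says.** **Intervention arm, months 0 to 4.** The Virtual visits section confines telecare to this arm: "Telemedicine visits in the intervention group will include telerehabilitation, neurologist and nurse telecare". It sets the frequency: "the nurse and the neurologist will conduct monthly video conferences with the patient". Falls are covered in the same contact as treatment adjustment: "During these visits, fall history and characteristics and medical management medications adjustments". The Procedure section ends this at month 4: "All patients allocated in the intervention group will discontinue the telemedicine program at the end of the" fourth month.

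**Both arms.** Under In-office visits: "Patients will be evaluated in-office at baseline, four months, and eight months". A falls history that includes the number of falls is part of each visit.

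**Sensor.** Blinded, remote motor assessments collects waist-sensor data, including falls, in all participants, "once a month during the eight months duration of the study". No wear period is given.

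**Primary outcome.** Outcome measures takes the total number of falls at 4 and at 8 months after randomisation. It does not say whether the count comes from the office history, the video-visit history, the sensor or a combination. Table 1 has no row for a fall count, only a falls-risk screen at screening.

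**Blinding.** The Statistical analysis section lists "blinded assessment of the results" among the safeguards. The investigator team has "two movement disorders MDS-UPDRS certified neurologists, two movement disorder nurses".

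**The concern.** A count of reported events depends on how often, and by whom, people are asked. For four months one arm is asked monthly by clinicians who also deliver its treatment. The other arm is asked by clinicians once, at the end. Randomisation balances the patients but not a questioning schedule that is set by allocation.

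The difference can reach the primary count in two ways:

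- Falls reported at video visits are added to the total.
- Only the month-4 office history is used, but intervention patients arrive at it having been prompted every month.

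The questioning gap closes when telemedicine stops. An apparent difference between short-term and long-term benefit could therefore partly reflect a change in ascertainment, and that comparison is one of the trial's aims. A cumulative 8-month total would carry over any difference from months 0 to 4.

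**Working it through.** **1. Contacts at which clinicians ask about falls, from the text**

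| Period | Intervention | Control |
|---|---|---|
| Months 0–4 | monthly video visits (up to 4) + month-4 office visit | month-4 office visit |
| Months 5–8 | month-8 office visit | month-8 office visit |
| Sensor, months 1–8 | once a month | once a month |

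The formal asymmetry is confined to the first phase. The sensor is common to both arms.

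**2. The plan's own figure.** The sample size is not in dispute. For 24% versus 2% responders (two-sided 5%, 80% power, pooled variance, no continuity correction):

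n = [1.96·√(2·0.13·0.87) + 0.842·√(0.24·0.76 + 0.02·0.98)]² / 0.22² ≈ 35.5, so 36 per arm and 72 in total, against 70 stated. Power at 35 per arm is 79.4%.

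**3. Effect on a rate ratio.** The protocol gives no recall rates, so these are assumptions. Let m be the extra proportion of falls missed in controls relative to the intervention arm.

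Observed ratio = true ratio / (1 − m)

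| m | true 1.0 reads | true 0.5 reads |
|---|---|---|
| 0 | 1.00 | 0.50 |
| 0.10 | 1.11 | 0.56 |
| 0.20 | 1.25 | 0.63 |
| 0.30 | 1.43 | 0.71 |

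These rows suppose that video-visit reports are counted and the sensor adds nothing. If only the office history is used, m is whatever monthly prompting adds to recall at month 4, and it could be small or zero.

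**4. Carry-over to 8 months.** Assume equal true falls in both halves and both arms, and the same four-month recall in both arms after month 4:

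Observed null ratio = [1 + (1 − m)] / [2(1 − m)]

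This gives 1.9/1.8 = 1.06, 1.8/1.6 = 1.13 and 1.7/1.4 = 1.21 for m = 0.10, 0.20 and 0.30.

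**5. Direction.** Suppose also that patients under-report to the team treating them by a proportion u. The null ratio becomes (1 − u)/(1 − m). With u = m it is 1.00. With u = 0.30 and m = 0.10 it is 0.7/0.9 = 0.78. With u = 0.10 and m = 0.30 it is 0.9/0.7 = 1.29. The sign depends on quantities the protocol does not give.

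**6. The responder endpoint.** The planned logistic model uses a 50% reduction in falls, yes or no. A simulation assumed a mean of 4 falls per 4 months, gamma-distributed patient rates (shape 1), Poisson counts, baseline recall 0.7 in both arms, at least one recorded baseline fall and a true rate ratio of 0.5. Intervention responders were 64% with follow-up recall also 0.7, 59% with 0.8 and 53% with 0.9. The levels depend on the assumed distribution and should not be set against the plan's 24% and 2%; only the direction and rough size of the change matter.

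On the plan's own scale, with controls at 2% and 35 per arm, erosion of 24% to 20% or 16% would lower power from 79% to 68% or 54%.

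**The case against.** **The source.** The video-visit sentence describes what the intervention consists of. It lists fall history beside education and referrals, and it is not under Study assessments. No sentence says these histories feed the primary count. The office history and the sensor run on the same schedule in both arms, and if either alone is the source, the formal schedule is equal. This stands. A reader might infer that the primary count does differ by arm, and the protocol does not support that. What remains is that the source is not fixed, and that monthly prompting can affect recall even at an identical visit.

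**The sensor.** A reader might infer that controls have no fall data between office visits. That is wrong, because the sensor covers all participants monthly. Without a wear period, however, neither a complete nor an incomplete count is established. Its collection is also described only for the study's eight months, so it does not supply the baseline side of the 50% reduction.

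**Blinding.** A reader might infer that blinded assessment fails because the team is small. This is not shown. The protocol claims blinded assessment, has two clinicians in each role, and nowhere says that the person delivering a patient's telecare also takes that patient's office fall history. Such a rota may be set out in the full protocol.

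**The size.** The ratios rest on assumed recall losses and on video-visit reports being counted. They are also on a rate-ratio scale, whereas the planned model uses the responder. All of this is correct, so the figures illustrate the risk and do not estimate it.

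**Conclusion.** The point holds in conditional form. Questioning about falls is unequal by arm in months 0 to 4, the source of the primary count is not fixed, and the one monthly source common to both arms is not described as a full count. The primary outcome is therefore open to differential ascertainment.

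If video-visit reports are counted and controls miss an extra 10% to 30% of falls, a null ratio would read 1.11 to 1.43 at 4 months, and 1.06 to 1.21 on a cumulative 8-month total under the assumptions in the working. If a common source is used and prompting has no effect, the distortion is nil.

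More frequent asking alone would work against the intervention, and a reader might conclude that the bias is therefore conservative. That does not follow, because under-reporting to the treating team could act the other way. This is a low-cost improvement to how the primary outcome is collected; it does not show that the result will be biased.

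**What to change.** - Give every participant the same monthly fall record for all eight months, for example a calendar returned with the monthly sensor data.
- Name that record as the only source of the primary count and of the follow-up side of the 50%-reduction responder.
- State that falls reported at video visits serve care only and do not enter the outcome.
- Have the month-4 and month-8 fall assessment recorded by the existing neurologist or nurse who does not deliver that patient's telecare, so that the claimed blinded assessment holds for this outcome.

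**Cost.** There is a slight burden on participants, and controls receive monthly attention to falls, which may itself change behaviour a little. The sensor section describes no monthly visit, so returning the record may need post or a short call. Baseline falls would still come from recalled history. If the monthly record catches more falls than recall does, fewer patients in either arm would meet the 50% criterion, but the measurement would be the same in both. The 24% and 2% planning rates should be reread in that light.

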## Study assessments

Extensive information on socio-demographic aspects, PD, comorbidity and treatment, and PD and gait dysfunction severity will be collected (Table 1). To avoid fatigue, we will recommend brief breaks to patients during assessments.

**Table 1 pone.0260889.t001:** Assessments.

	Screening	Baseline	4-Month Visit	8-Month Visit
Sociodemographics	✓			
Falls risk screening	✓			
Montreal Cognitive Assessment	✓			
MDS-Unified Parkinson’s Disease Rating Scale		✓	✓	✓
Hoenh & Yahr Stage		✓	✓	✓
Freezing of Gait Questionnaire		✓	✓	✓
Non-Motor Symptoms Scale		✓	✓	✓
Parkinson’s Disease Sleep Scale		✓	✓	✓
Visual Analog Scale-Pain		✓	✓	✓
Visual Analog Fatigue Scale		✓	✓	✓
Beck Depression Inventory-II		✓	✓	✓
Lille Apathy Rating Scale		✓	✓	✓
Schwab & England Activities of Daily Living Scale		✓	✓	✓
European Health Interview Survey-Quality of Life 8 item index		✓	✓	✓
Cumulative Illness Rating Scale for Geriatrics		✓	✓	✓
Cost questionnaire for patients with PD.		✓	✓	✓
Parkinson’s disease Quality of Life-39		✓	✓	✓
Malnutritional Universal Screening Tool		✓	✓	✓
Eating Assessment Tool		✓	✓	✓
European Quality of Life 5 Dimensions		✓	✓	✓
Zarit Caregiver Burden Inventory		✓	✓	✓
Mini Balance Evaluation Systems Test		✓	✓	✓
Timed Up and Go Test		✓	✓	✓
Frail Scale		✓	✓	✓
Fried Frailty Index		✓	✓	✓
Falls Efficacy Scale-International		✓	✓	✓
Telehealth Usability Scale				✓
Quebec User Evaluation of Satisfaction with Assistive Technology				✓

### In-office assessments

1) Nutritional, sarcopenia status, and frailty status: We will assess anthropometrics: body mass index (BMI) calculated by the following formula: weight (kg)/height^2^ (m^2^), screening for malnutrition with the Malnutritional Universal Screening Tool [MUST] [30], presence of dysphagia using the Eating Assessment Tool (EAT-10) [31], presence of sarcopenia based on standard bioimpedance (BC418MA, mono frequency, Tanita UK^®^, Yiewsley, UK) with the following cut-off parameters [men: severe sarcopenia with an appendicular skeletal mass < 15 kg, appendicular skeletal mass/height < 7 Kg/m^2^, women: severe sarcopenia with an appendicular skeletal mass < 15 Kg, appendicular skeletal mass/height < 5.5 Kg/m^2^] [32–34]. and handgrip strength (Jamar ^®^ Plus hydraulic hand dynamometer, cutoff for men: < 30 Kg, and for women: < 20 Kg) [35], and frailty using the Fried Frailty Index (FRIED) [36].

2) PD motor and non-motor symptoms severity will be assessed using the MDS-UPDRS [37], Non-Motor Symptoms Scale (NMSS) [38], Parkinson’s Disease Sleep Scale (PDSS) [39], Visual Analog Scale-Pain (VAS-Pain) [40], Visual Analog Fatigue Scale (VAFS) [41], Beck Depression Inventory-II (BDI-II) [42], Lille Apathy Rating Scale (LARS) [43], Schwab & England Activities of Daily Living Scale (ADLS) [44].

3) Patient’s health-related quality, caregiver burden, and comorbidities will be assessed using the Quality of life European Health Interview Survey-Quality of Life 8 item index [EUROHIS-QOL 8 item-index] [45]; the Parkinson’s disease summary index score (PDQ-39) [46], Zarit Caregiver Burden Inventory (ZCBI) [47], and the Cumulative Illness Rating Scale for Geriatrics (CIRS-G) [48].

4) Gait and postural balance impairment will be assessed using the Mini Balance Evaluation Systems Test (MINI-BEST) [49], Timed Up and Go Test (TUG and COG-TUG) [50], Frail Scale (FRAIL) [51], Falls Efficacy Scale-International (FES-I) [52], and Freezing of Gait Questionnaire (FOGQ) [53].

5) Cost of telemedicine delivery and health service use: Implementing the telemedicine program will account for the cost of equipment supplied and the average hospital wage for health personnel services. Data on health service utilization will be assessed, including direct medical costs (medical visits, hospitalization, use of other physical therapies at the end of the intervention phase, goods and services used, diagnosis, or treatment), and non-medical costs (e.g., paid caregivers, transportation, social services, paid caregivers, adaptation of accommodation, and any special equipment).

6) Satisfaction: Patient satisfaction in terms of usability of telehealth implementation and services will be measured using the telehealth usability questionnaire (TUQ) and the Quebec user evaluation of satisfaction [54, 55].

### Blinded, remote motor assessments

In all participants, we will collect waist-worn wearables data reporting On and Off states (with and without dyskinesias), gait parameters, falls and FOG using the STAT-ON™, once a month during the eight months duration of the study.

## Technology for videoconferencing and artificial intelligence

The telerehabilitation system presented in this study is composed of the server (Jitsi) through which the data are relayed, an affordable device that patients can use at home, a home television, and an additional server for applying the Artificial Intelligence (AI) techniques including Kafka, Spark, and Detectron2. All the source code of the telerehabilitation system is publicly available on Github:https://github.com/admirable-ubu/FIS-FBIS/

## Statistical analysis

### Sample size

We calculated the sample size using the Epidat^®^ 4.1 statistical software. Considering that a 50% fall reduction in the number of falls compared to baseline will be obtained in 24% of the participants in the intervention group and 2% in the control group, we estimated that 70 patients (35 per group) would provide 80% power (5% probability of type 1 error) with a confidence level of 95%. By assuming a 9% dropout rate, a total sample of 76 patients will be then included in this study.

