## Background

The Parkinson’s disease (PD) population is mainly sedentary, causing a dramatic reduction of physical activity compared to healthy older adults, even early in the disease [1, 2]. As PD progresses, falls are often harmful and very common [3]. Approximately 40–70% of people with PD fall each year, and one-third fall repeatedly [3, 4]. twice as likely as the healthy elderly population [5]. Evidence shows that falls significantly impact people’s lives with PD, including debilitating effects on confidence, decreased activity levels, and reduced quality of life [6–8]. Consequently, repeat falls are a risk factor that implies subsequent falls, often with such consequences as fractures, prolonged immobility and dependency, social isolation, and financially costly individuals and healthcare systems [9].

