### Study population

We will invite non-demented, ambulatory patients aged > 18 years old, with established idiopathic PD based on the MDS-criteria [22, 23], with a medium-high risk of falling established by a history of at least one fall in the previous 12 months with a Hoehn & Yahr (HY) stage < 3 [24], a Montreal Cognitive Assessment (MoCA) score > 18 [25], without access to non-pharmacological therapies, and one of the two additional criteria including the presence of freezing of gait (FOG) or self-selected gait speed < 1.1 meters/second [26]. We will exclude patients with severe psychiatric or cerebrovascular diseases, severe traumatic head injuries, severe orthopedic lower limb or spine problems, peripheral neuropathy, rheumatological disease, or other systemic diseases or sensory deficiencies that, according to the investigator’s judgment, may interfere with the study.

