### Outcome measures

The study’s primary outcome measure will be the total number of falls in the 4-month (short-term benefit) and 8-month (long-term benefit) after randomization. A fall will be defined as unintentionally coming to rest on the ground or other lower surface without overwhelming external force or a major internal event [56].

Other secondary outcome measures will include: 1) Cost-effectiveness, which will be estimated using natural units of health outcomes, including the incremental cost-effectiveness ratio per fall prevented and cost per extra person avoiding mobility deterioration (identified as an average number of daily steps assessed by wearable sensors); 2) A cost-utility analysis using the EuroQoL will estimate the incremental cost per quality-adjusted life-years (QALY) gain; 3) Short and long-term rate of change from baseline to four and eight months, respectively of motor, NMS, gait, balance, HR-QoL, caregiver burden, and comorbidities severity; 4) Feasibility (completed telemedicine visits) and adherence (dropout rate of telemedicine visits).

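### The 2% control response behind the sample size does not fit the trial's own entry and responder rules, so the stated 80% power is unsupported

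*Protocol article*

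**What the plan says.** The Sample size section rests on this assumption: "a 50% fall reduction in the number of falls compared to baseline will be obtained in 24% of the participants in the intervention group and" (the sentence goes on to give 2% for controls). From this, "we estimated that 70 patients (35 per group) would provide 80% power (5% probability of type 1 error"). No source is given for either percentage.

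The Statistical analysis section carries the same event into its logistic model, with a "50% reduction in the incidence of falls (yes vs. no) as the dependent variable". Neither section gives a minimum baseline count or says over which period baseline falls are counted.

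The Study population section admits patients with "a history of at least one fall in the previous 12 months", plus freezing of gait or slow gait. This is the only pre-study fall window in the article. Follow-up falls are "the total number of falls in the 4-month (short-term benefit) and 8-month (long-term benefit) after randomization" (Outcome measures). The only fall frequencies given are in the Background: "Approximately 40–70% of people with PD fall each year, and one-third fall repeatedly".

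**The concern.** A responder rule based on a 50% drop behaves badly when counts are low. With one fall in 12 months, half the baseline rate is 0.17 falls over 4 months or 0.33 over 8 months, so the patient responds simply by not falling. Patients with higher counts have more room, but the same chance variation works on them. In addition, everyone is selected for having fallen, so follow-up counts tend to be lower than baseline without any treatment. Converting both windows to a monthly rate does not remove this.

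A 2% response among untreated patients says that almost none of this happens. The stated power depends on that near-zero value: moving the control rate towards the middle of the scale raises the variance of the comparison, and the assumed 24% in the intervention group loses its meaning as a target.

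**Working it through.** **1. The plan's own figure.** Inputs: 24% and 2%, 35 per group, 5% type 1 error (taken as two-sided; the article does not say). With p̄ the mean of the two proportions,

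power = Φ{ [ |p1 − p0|·√n − 1.96·√(2p̄(1 − p̄)) ] / √(p1(1 − p1) + p0(1 − p0)) }.

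Here p̄ = 0.13, so power = Φ{ (0.22 × 5.916 − 1.96 × 0.4756) / 0.4494 } = Φ(0.82) = 79.4%. The matching sample size is 36 per group. The stated 35 per group and 80% therefore reproduce to within rounding.

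**2. Chance response for one patient.** For a single faller with a true rate of 1.5 falls a year, the probability of no falls is exp(−1.5 × 4/12) = 61% over 4 months and exp(−1.5 × 8/12) = 37% over 8 months.

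**3. Chance response for the whole cohort.** Assumptions: a stable personal rate, unchanged by treatment; baseline count X over 12 months, kept if X ≥ 1; follow-up count Y over t months; response if Y/t ≤ 0.5·X/12. Counts are Poisson given the personal rate. That rate is either the same for all patients or gamma-distributed with shape k and mean m per year.

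Three of the gamma cases are fitted to the Background, taking one-third as the share of all patients who fall repeatedly. The proportion falling in a year is set at 40%, 55% and 69%, to span the article's 40–70%. The other rates are assumed. The halved-rate columns apply a rate ratio of 0.5 in the intervention group, and power uses the formula in step 1 with n = 35.

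| Case | Mean falls/year, eligible | Single fallers | No-effect response, 4 / 8 months | Response at halved rate, 4 / 8 months | Power for halving, 4 / 8 months |
|---|---|---|---|---|---|
| Background, 69% fall | 1.7 | 52% | 67% / 52% | 82% / 72% | 29% / 42% |
| Background, 55% fall (k = 0.74, m = 1.44) | 2.6 | 40% | 58% / 47% | 75% / 70% | 34% / 49% |
| Gamma, k = 1, m = 3 | 4 | 25% | 46% / 36% | 68% / 64% | 47% / 66% |
| Gamma, k = 1, m = 6 | 7 | 14% | 35% / 26% | 63% / 60% | 64% / 84% |
| Gamma, k = 1, m = 12 | 13 | 8% | 26% / 18% | 59% / 57% | 83% / 95% |
| Background, 40% fall | 22 | 18% | 32% / 24% | 64% / 61% | 77% / 89% |
| Same rate in all, 12 a year | 12 | under 1% | 18% / 10% | 56% / 55% | 92% / 99% |

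No-effect response runs from 10% to 67%.

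**4. What 2% would require.** Even with no variation between patients, which is the most favourable case, response falls to 2.0% only at about 28 falls a year in every patient (8 months) or about 50 (4 months). With gamma variation (k = 1) and a mean of 30 a year it is still 15% at 4 months and 9% at 8 months.

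**5. Power if the planned 22-point difference is kept.** With 35 per group:

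| Control rate | Power | Needed per group for 80% |
|---|---|---|
| 2% | 79% | 36 |
| 18% | 53% | 66 |
| 30% | 46% | 78 |
| 38% | 45% | 80 |
| 58% | 51% | 69 |

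**The case against.** A reader might infer that the trial is shown to be underpowered. The article does not support that. Carrying 22 points over to a new control rate is itself a choice. If the planned odds ratio of (0.24/0.76)/(0.02/0.98) = 15.5 were kept instead, power would exceed 97%, although that implies 77–96% responders in the intervention group. For a halved fall rate, several cases reach or pass 80%, mostly at 8 months. The Background describes Parkinson's disease in general, whereas the trial enrols a higher-risk group, and the article gives no per-patient fall rate. All of this stands.

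A reader might also blame single fallers for the whole range. They are only a minority in most of the cases above, and chance response persists at higher counts; the 10–67% covers all baseline counts.

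Two inputs are uncertain. The 12-month baseline is inferred. Also, baseline falls come from history, while follow-up adds monthly sensor data; fuller capture at follow-up would lower the no-effect response.

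Finally, chance responders occur in both randomised groups, and the logistic model compares those groups. The comparison is therefore not biased, and the article nowhere proposes to read the responder share in one group as benefit. This limits the point to the planning figures. None of it brings the 2% within reach, since even a uniform 12 falls a year leaves 10% at 8 months.

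**Conclusion.** The 2% control response is incompatible with entry on one fall in 12 months combined with a 50% reduction rule. Chance and selection alone give about 10–67% responders. This rests on a stable personal fall rate, a 12-month baseline, equal capture of falls in both periods and comparison as monthly rates.

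The 80% power rests on the 2% and is therefore unsupported, which is not the same as shown to be wrong. At control rates of 18–58% with a 22-point difference, power is about 45–53%. For a true halving, with rates differing between patients, it runs from 29% (34% with the mid-range Background fit) to 83% at 4 months, and from 42% (49%) to 95% at 8 months. It is higher still if all patients share a high rate. The planned 24% is equally out of line, because a halved rate gives 55–82% responders in the cases above.

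**What to change.** In the Sample size section, replace the 2% and 24% with response rates derived from a stated fall distribution for eligible patients. Declare that distribution as an assumption, include chance variation and name the baseline window. Then give the power of 35 per group as a range for a named fall-rate ratio at both 4 and 8 months. For example, for a ratio of 0.5 and gamma-distributed rates averaging 2.6 to 13 falls a year among eligible patients, the text would report control response of 58% to 26% with power of 34% to 83% at 4 months, and 47% to 18% with power of 49% to 95% at 8 months. The sponsor should substitute its own distribution if it has one.

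Enrolment stays at 76 and the logistic model does not change. The cost is a rewritten paragraph and a short calculation. The downside is a stated power that is less favourable and less certain.
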